### Serious adverse events

4.2

Serious adverse events (SAEs), defined as events that result in death, are life-threatening, require hospitalization or prolongation of existing hospitalization, result in persistent or significant disability/incapacity, or are considered medically important, will be reported to the Institutional Review Board (IRB) and Data Safety Monitoring Board (DSMB) within 24 h of the study team becoming aware of the event. Causality assessment will be performed by the principal investigator and verified by an independent physician.

### Data safety monitoring board

4.3

An independent DSMB will be established to monitor participant safety and study conduct. The DSMB will consist of at least three members with expertise in clinical trials, neurorehabilitation, and biostatistics, none of whom have direct involvement in the study. The DSMB will meet after enrollment of 20, 40, and 60 participants to review safety data and may recommend modifications to the study protocol or early termination if safety concerns arise. Pre-specified stopping rules will be established based on the incidence of serious adverse events. All TMS procedures will adhere to international consensus guidelines for the safe use of transcranial magnetic stimulation (Rossi et al., 2021).

## Statistical analysis

5

### Analysis populations

5.1

The intention-to-treat (ITT) population will include all randomized participants, analyzed according to their assigned treatment group regardless of protocol adherence. This will serve as the primary analysis population. The per-protocol (PP) population will include participants who complete at least 80% of scheduled treatment sessions and all primary outcome assessments. The safety population will include all participants who receive at least one treatment session.

### Primary analysis

5.2

The primary analysis will compare change in LEMS from baseline to Week 16 between treatment groups using analysis of covariance (ANCOVA), with baseline LEMS, AIS grade, neurological level of injury, and study site as covariates. The treatment effect will be estimated as the adjusted mean difference between groups with corresponding 95% confidence interval. Statistical significance will be determined at the two-sided α = 0.05 level.

Missing data for the primary outcome will be handled using multiple imputation under the missing-at-random assumption. Sensitivity analyses will include complete-case analysis, last-observation-carried-forward, and pattern-mixture models to assess the robustness of findings under different missing data mechanisms.

### Secondary analyses

5.3

Secondary outcomes (10MWT, 6MWT, SCIM-III, MAS) will be analyzed using similar ANCOVA models. For outcomes measured at multiple time points (baseline, Week 8, Week 16, and Week 20), mixed-effects models for repeated measures (MMRM) will be used to characterize the trajectory of change over time and assess treatment-by-time interactions.

Responder analyses will compare the proportion of participants achieving clinically meaningful improvements (≥2 points LEMS, ≥0.1 m/s 10MWT speed) between groups using chi-square tests or Fisher's exact test as appropriate.

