### Primary outcome

3.1

The primary outcome measure is change in Lower Extremity Motor Score (LEMS) from baseline to Week 16, the immediate post-intervention timepoint (Table 3). Week 16 was selected as the primary endpoint because it captures the maximal cumulative effect of the combined neuromodulation protocol following completion of all 32 sessions, aligns with established convention in TMS and tSCS rehabilitation trials (Benito et al., 2012; Kumru et al., 2016; Feng et al., 2023; Shi et al., 2025), and minimizes confounding from post-intervention behavioral variability (e.g., changes in physical activity or unsupervised practice) that may differentially affect the two arms during follow-up. Week 20 is retained as a pre-specified secondary time-point to assess durability of treatment effects within the MMRM framework (Section 5.3).

**Table 3 T3:** Summary of outcome measures.

Outcome	Type	Measurement tool	Clinical significance
Lower extremity motor score	Primary	ISNCSCI (0–50 points)	MCID: 2–3 points; predicts ambulation
Walking speed	Secondary	10MWT (m/s)	MCID: 0.15 m/s
Walking endurance	Secondary	6MWT (meters)	MCD: 45.8 meters; MCID estimates range 30–50 meters
Functional independence	Secondary	SCIM-III (0–100)	Comprehensive SCI-specific measure
Quality of life	Secondary	EQ-5D-5L	Health utility index and EQ-VAS; validated in SCI populations
Spasticity	Secondary	Modified Ashworth Scale (0–4)	Clinician-rated muscle tone
Corticospinal excitability	Exploratory	MEP amplitude/latency	Neurophysiological plasticity marker
EMG	Exploratory	EMG activity	Muscle activity/recruitment

ISNCSCI, International Standards for Neurological Classification of Spinal Cord Injury; 10MWT, 10-Meter Walk Test; 6MWT, 6-Minute Walk Test; SCIM-III, Spinal Cord Independence Measure-III; MEP, Motor Evoked Potential; MCID, Minimal Clinically Important Difference.

The LEMS is a component of the International Standards for Neurological Classification of Spinal Cord Injury (ISNCSCI), representing the summed strength of five key muscle groups in each lower extremity (hip flexors, knee extensors, ankle dorsiflexors, great toe extensors, and ankle plantarflexors), graded on a 0–5 scale for each muscle group. The total LEMS ranges from 0 to 50 points, with higher scores indicating greater motor strength (Kirshblum et al., 2011).

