### Secondary outcomes

3.2

All secondary outcomes will be assessed at baseline, Week 8, Week 16, and Week 20, with the exception of MEP assessments, which will be conducted at baseline, Week 16 and Week 20 only, as shown in Table 2.

**Walking Function:** The 10-Meter Walk Test (10MWT) will assess walking speed over a 10-meter distance at both comfortable and maximum speeds, with excellent reliability (inter-rater *r* = 0.97, intra-rater *r* = 0.98) established for SCI populations (Jackson et al., 2008). The 6-Minute Walk Test (6MWT) will measure walking endurance as the total distance walked in 6 min on a standardized course (Lam et al., 2008). The type and level of assistive device used during baseline assessment of the 10MWT and 6MWT (e.g., rolling walker, forearm crutches, cane, or no device) will be documented and standardized across all subsequent assessment time points to ensure reproducibility and valid within-participant comparisons.

**Functional Independence:** The Spinal Cord Independence Measure-III (SCIM-III) is a disability scale specifically developed for persons with SCI, assessing self-care (0–20 points), respiration and sphincter management (0–40 points), and mobility (0–40 points). The total score ranges from 0 to 100, with higher scores indicating greater independence (Catz et al., 2007).

**Quality of Life:** The EQ-5D-5L (EuroQol Group) will be administered to capture participant-perceived health status across five dimensions: mobility, self-care, usual activities, pain/discomfort, and anxiety/depression, along with a visual analog scale (EQ-VAS) for overall health. The EQ-5D-5L is widely validated in SCI populations, is brief to administer, and generates utility values that can support future health economic evaluations of the intervention (Herdman et al., 2011).

**Spasticity:** The Modified Ashworth Scale (MAS) will be used to assess spasticity in bilateral hip flexors, knee extensors, and ankle plantarflexors, graded from 0 (no increase in tone) to 4 (limb rigid in flexion or extension).

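### The 10MWT responder cut-off of 0.1 m/s lies below the protocol's own MCID of 0.15 m/s, and nothing reconciles the two

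*Protocol article*

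**What the plan says.** Section 5.3 (Secondary analyses) plans a dichotomised comparison next to the continuous analyses: "Responder analyses will compare the proportion of participants achieving clinically meaningful improvements", with the cut-offs "≥2 points LEMS, ≥0.1 m/s 10MWT speed". The proportions are to be compared "between groups using chi-square tests or Fisher's exact test as appropriate".

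Table 3 (Section 3.1) has a column on clinical significance. For the 10MWT it gives one MCID, 0.15 m/s, with no range. For LEMS it gives "MCID: 2–3 points; predicts ambulation". For the 6MWT it gives MCID estimates of 30 to 50 metres. The table footnote spells out the abbreviation: "MCID, Minimal Clinically Important Difference".

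No section derives, cites or explains the 0.1 m/s figure, and none comments on how it differs from Table 3.

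**The concern.** An MCID is, by its name, the smallest change regarded as clinically important. If it is 0.15 m/s for this test, a gain of 0.10 m/s is not clinically meaningful on the same scale. The article makes both statements about the same measure.

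The purpose of a responder analysis is to put clinical meaning on a result. Readers will take the published proportion as the share of participants who benefited to a degree that matters. If part of that share rests on gains below the trial's own MCID, the proportion cannot be read as labelled, and anyone who compares the results with Table 3 will see the mismatch. The conflict is easy to settle now and hard to settle credibly once results are known.

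**Working it through.** **Inputs from the article**

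- 10MWT responder cut-off: 0.10 m/s (Section 5.3)
- 10MWT MCID: 0.15 m/s (Table 3)
- LEMS responder cut-off: 2 points (Section 5.3); LEMS MCID: 2 to 3 points (Table 3)
- Planned enrolment: 30 per group (Section 2.3)

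The article states no responder rate, power or SD for walking speed, so there is no calculated figure to reproduce.

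**Step 1: compare the thresholds.** 0.15 − 0.10 = 0.05 m/s, and 0.10 / 0.15 = 0.67. The cut-off is two thirds of the MCID. The LEMS cut-off of 2 lies inside its Table 3 range, so of the two responder thresholds only the walking-speed one conflicts with the table.

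**Step 2: how many participants fall in the disputed band.** Assume that individual change X is normal with mean m and SD s. Both are assumptions, shown over a range. Then P(X ≥ c) = 1 − Φ((c − m)/s). The band is P(X ≥ 0.10) − P(X ≥ 0.15), and its share of responders is the band divided by P(X ≥ 0.10).

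Example with m = 0.10 and s = 0.15: P(X ≥ 0.10) = 1 − Φ(0) = 0.500. P(X ≥ 0.15) = 1 − Φ(0.333) = 0.369. The band is 0.131, and its share is 0.131 / 0.500 = 26%.

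| m | s | P(X ≥ 0.10) | P(X ≥ 0.15) | Band | Share of responders |
|---|---|---|---|---|---|
| 0 | 0.10 | 0.159 | 0.067 | 0.092 | 58% |
| 0 | 0.15 | 0.252 | 0.159 | 0.094 | 37% |
| 0 | 0.20 | 0.309 | 0.227 | 0.082 | 27% |
| 0.05 | 0.10 | 0.309 | 0.159 | 0.150 | 49% |
| 0.05 | 0.15 | 0.369 | 0.252 | 0.117 | 32% |
| 0.05 | 0.20 | 0.401 | 0.309 | 0.093 | 23% |
| 0.10 | 0.10 | 0.500 | 0.309 | 0.191 | 38% |
| 0.10 | 0.15 | 0.500 | 0.369 | 0.131 | 26% |
| 0.10 | 0.20 | 0.500 | 0.401 | 0.099 | 20% |
| 0.15 | 0.10 | 0.691 | 0.500 | 0.191 | 28% |
| 0.15 | 0.15 | 0.631 | 0.500 | 0.131 | 21% |
| 0.15 | 0.20 | 0.599 | 0.500 | 0.099 | 17% |

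The band runs from 8 to 19 percentage points. With 30 per group that is 30 × 0.082 = 2.5 to 30 × 0.191 = 5.7 participants per arm.

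**Step 3: the comparison between arms.** If both arms have the same distribution of change, the expected difference in proportions is zero at either cut-off, so neither creates a false difference. Suppose instead that s = 0.15 and the arm means are 0.05 and 0.10. The difference between arms is 0.500 − 0.369 = 0.131 at the lower cut-off and 0.369 − 0.252 = 0.117 at the higher. In this example each arm's rate moves by 12 to 13 points, but the contrast moves by only about 1.

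**The case against.** The strongest reply is that the document does not show which number is wrong. Section 5.3 is itself a protocol statement of what counts as meaningful, and Table 3 is a descriptive summary, not an analysis rule. That stands. A reader might infer that 0.15 m/s is the true value and that participants between the cut-offs are misclassified. The article derives neither figure, so it supports only the statement that the two disagree.

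Three other stronger readings also fail.

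- **An open choice of threshold.** A reader might infer that the analyst could pick either value after seeing the data. Section 5.3 fixes one cut-off, so the planned analysis is determinate. What conflicts is its label.
- **A biased comparison.** A reader might take the higher responder rates as favouring the intervention. The cut-off is common to both arms, so no bias or inflation of type I error follows.
- **An undefined walking speed.** The 10MWT "will assess walking speed over a 10-meter distance at both comfortable and maximum speeds" (Section 3.2), and the responder rule does not name one. This is detail that a condensed article may leave to the analysis plan, which is not shown. It is not part of this point.

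It is also fair to say that the consequence is limited: one responder analysis of one secondary outcome. None of this removes the contradiction. A condensed article may omit details, but here it prints two incompatible values, and an analysis plan that adopts either would still disagree with the other.

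**Conclusion.** The inconsistency is real and rests wholly on the article's own figures: a change called clinically meaningful in Section 5.3 is one third smaller than the MCID in Table 3, without explanation. Under the assumed normal changes in the grid, the two cut-offs give responder proportions about 8 to 19 percentage points apart, and about 17% to 58% of those counted as responders would fall below the stated MCID. These figures depend on assumed means and SDs and only illustrate the scale. The contradiction itself does not depend on them.

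The effect is on the interpretation of each arm's 10MWT responder rate. Type I error, the primary LEMS ANCOVA, the LEMS responder analysis and the continuous 10MWT models are unaffected. It should be corrected, but it does not threaten the trial's main conclusion.

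**What to change.** Use one threshold for clinically meaningful change on the 10MWT throughout, and settle it before unblinding. The default is to set the cut-off in Section 5.3 to at least 0.15 m/s so that it agrees with Table 3, keeping at least 0.1 m/s as a labelled sensitivity analysis if wanted. The alternative is to keep 0.1 m/s, correct the Table 3 entry and give the justification for the lower value.

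Either route is a one-line change with no effect on sample size, visits or data collection. The default has one small downside: the reported responder rate will be lower, or at most equal, in both arms.

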### Subgroup analyses

5.4

Pre-specified subgroup analyses will examine treatment effects according to baseline LEMS (10–30 vs. 31–45), AIS grade (C vs. D), neurological level (cervical vs. thoracic), time since injury (12–36 months vs. >36 months), study site (NUH vs. Alexandra Hospital), and baseline ambulatory status (non-ambulatory vs. ambulatory with assistance). Subgroup analyses will be considered exploratory and interpreted with appropriate caution given the limited sample size for detecting interaction effects. An additional exploratory subgroup analysis will compare treatment effects between participants in whom MEPs are present at baseline vs. those in whom MEPs cannot be reliably elicited. This analysis will explore whether preservation of corticospinal tract conduction is a prerequisite for, or modifier of, treatment response to combined TMS-tSCS.

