### Study population

2.2

Participants will be recruited from the rehabilitation departments at National University Hospital and Alexandra Hospital, Singapore. Recruitment strategies will include physician referrals, review of electronic medical records for potentially eligible patients, and outreach through spinal cord injury support groups and community organizations in Singapore.

A baseline LEMS threshold of >10 was selected to ensure participants retained sufficient residual motor function to engage meaningfully with the rehabilitation protocol and to demonstrate measurable changes on motor and walking outcome measures. This threshold corresponds to at least some volitional movement in multiple lower extremity muscle groups, which is a prerequisite for task-specific training during tSCS sessions (Table 1).

**Table 1 T1:** Eligibility criteria.

Inclusion criteria	Exclusion criteria
1. Age 18–65 years at enrollment	1. History of seizures or epilepsy
2. Chronic traumatic SCI (≥12 months post-injury)	2. Implanted electronic devices (pacemaker, cochlear implant, DBS, and spinal cord stimulator)
3. Incomplete injury (AIS grade C or D)	3. Metallic implants in head or spine
4. Neurological level of injury C2–L1	4. Pregnancy or planned pregnancy
5. Baseline LEMS > 10 points	5. Active psychiatric disorder or cognitive impairment
6. Medically stable	6. Concomitant neurological conditions (stroke, TBI, neuropathy)
7. Able to provide informed consent	7. Skin breakdown at electrode sites
8. Able to commit to full study duration	8. Current participation in another trial
9. Able to attempt the 10-Meter Walk Test and 6-Minute Walk Test with or without assistive devices and standby assistance	9. History of skull surgery or craniotomy
	10. Medications altering cortical excitability (within 2 weeks)

SCI, Spinal Cord Injury; AIS, American Spinal Injury Association Impairment Scale; LEMS, Lower Extremity Motor Score; DBS, Deep Brain Stimulator; TBI, Traumatic Brain Injury.

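### Section 5.4 examines baseline LEMS and time since injury only as two-band subgroups; a continuous interaction term would be more efficient if effect modification is roughly linear

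*Protocol article*

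**What the plan says.** Section 5.4 (Subgroup analyses) lists the pre-specified subgroups. Two of them come from variables with many possible values: "treatment effects according to baseline LEMS (10–30 vs. 31–45") and "time since injury (12–36 months vs. >36 months"). Each is given as two bands, and no other form is mentioned. On their status the section says: "Subgroup analyses will be considered exploratory and interpreted with appropriate caution given the limited sample size for detecting interaction effects".

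Both variables are finer than the bands. Section 3.1 states "The total LEMS ranges from 0 to 50 points", and Table 1 sets entry at "Baseline LEMS > 10 points" with no upper limit. Table 1 also requires "Chronic traumatic SCI (≥12 months post-injury"), again with no upper limit.

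Two other places bear on the point. The LEMS bands repeat the randomisation strata of Section 2.4; time since injury is not a stratification factor. The primary ANCOVA in Section 5.2 is adjusted "with baseline LEMS, AIS grade, neurological level of injury, and study site as covariates". No banding of LEMS is stated there, and time since injury is not among the covariates.

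**The concern.** A two-band split treats LEMS 11 and 30 as alike and 30 and 31 as different. If benefit rises or falls gradually with residual motor function or with chronicity, comparing two band averages uses only part of that gradient, and the answer depends on where the cut falls. No basis is stated for 36 months.

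These subgroups can tell a later trial whom the combined stimulation helps. A protocol that already warns of limited ability to detect interactions gains from using the full scale of variables it will have on file. At stake is the usefulness of an exploratory result, not the primary conclusion.

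**Working it through.** **Plan's own figure.** The protocol gives no interaction power, no distribution for either modifier and no figure for information lost, so there is nothing to reproduce.

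**Inputs from the protocol (Section 2.3).** SD 4.5; 60 enrolled; 20% dropout, so 60 × 0.8 = 48 evaluable; planned difference 2 points; two-sided α = 0.05. I take these as given here.

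**Assumed, not in the protocol.** The distributions of LEMS and of time since injury, a linear gradient, and its size.

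**Step 1: information kept by a split.** Under a linear gradient, the share kept relative to a linear term is the squared correlation between the modifier X and the indicator X > c. With p the share below the cut:
- Normal X: φ(c)² / [p(1−p)]. At the median, 0.159 / 0.25 = 0.637, a loss of 36%.
- Uniform X: 3p(1−p). At the median, 3 × 0.25 = 0.75, a loss of 25%.
- 70/30 split: 0.576 (normal) and 0.63 (uniform), losses of 42% and 37%.
- 80/20 split: 0.49 and 0.48, losses of 51% and 52%.

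For LEMS cut at 30, the loss is about 25% if uniform over 11–50, 27% if uniform over 11–45, and 32–43% for truncated normal shapes with mean 25–38 and SD 9–10. For time since injury cut at 36 months, the assumed right-skewed distributions give losses of 31–72% for a gradient linear in log months. If the true modification is a step exactly at the cut, the banded form loses nothing.

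**Step 2: analytic power.** With 1:1 allocation, the standard error of a linear interaction per SD of the modifier is 2σ/√N.
- N = 60: 9/√60 = 1.162. For 3 points per SD the noncentrality is 3/1.162 = 2.58, power 0.72. Multiplying by √0.637 gives 2.06, power 0.53.
- N = 48: 9/√48 = 1.299. The noncentrality is 2.31, power 0.62; banded 1.84, power 0.44.

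**Step 3: simulated power.** Normal LEMS, mean 30, SD 8, residual SD 4.5, interaction linear per SD of LEMS, bands cut between 30 and 31:

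| Interaction per SD | N=48 continuous | N=48 banded | N=60 continuous | N=60 banded |
|---|---|---|---|---|
| 3 points | 58% | 40% | 69% | 49% |
| 2 points | 30% | 20% | 37% | 25% |
| 1 point | 12% | 9% | 12% | 10% |

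Simulation error is a point or two; repeat runs at 1 point per SD gave 11–14% against 9–11%. The values sit slightly below Step 2, which ignores chance variation in the modifier's spread within each arm and, for the banded form, the within-band gradient left in the residual. For LEMS uniform over 11–45 at 3 points per SD and N = 48, power is about 59% against 45%.

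**Step 4: how large these interactions are.** With the planned average effect of 2 points, 3 points per SD means an effect of 2 − 3 = −1 one SD below mean LEMS and 2 + 3 = 5 one SD above. At 1 point per SD the effects are 1 and 3.

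**Step 5: the bands in absolute terms.** With two equal bands, the difference in treatment effects detectable with 80% power is 2.80 × 4σ/√N. This is 2.80 × 18/√60 = 6.5 points at N = 60 and 2.80 × 18/√48 = 7.3 points at N = 48, against a planned main effect of 2.

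**The case against.** The strongest reply is that Section 5.4 is one paragraph of a journal article. It names subgroups and states no model. It neither mentions nor excludes a continuous interaction, and the analysis plan may contain one. A reader might infer that the protocol commits to an inefficient interaction test; the text does not support that, because it specifies no test. What stands is that the bands are the only form the protocol pre-specifies, and its own warning about interactions is a reason to name the more efficient form there.

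Second, the LEMS bands are not arbitrary: they are the randomisation strata, and showing effects by stratum is conventional. This justifies displaying them, but not relying on them alone. It does not extend to the 36-month cut.

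Third, the subgroups are exploratory and the discussion in Section 7 repeats the sample-size limitation. This stands in full and keeps the point minor.

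Fourth, the power gain is visible only for large interactions. This also stands: 3 points per SD exceeds the planned main effect, and at 1 point per SD the change gains only a few percentage points.

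A reader might also quote about 78% against 62% for a uniform LEMS at N = 48. Those figures arise from 3 points per 8 LEMS points. A uniform 11–45 score has SD √[(35² − 1)/12] = 10.1, so they correspond to 3 × 10.1/8 = 3.8 points per SD and cannot be set beside the 3-point normal case.

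**Conclusion.** The point holds as a minor improvement to an exploratory analysis. If modification is roughly linear, the two-band form gives up about 25–36% of the information at a median cut and more at an off-centre one. In the normal-LEMS illustration, the continuous form gains 18 percentage points of power at N = 48 and 20 at N = 60 for 3 points per SD, about 10–12 for 2 points, and almost nothing for 1 point.

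A reader might infer that a loss of a quarter to a third is a property of this trial. It is not: it needs a linear gradient, a cut near the median and a uniform-to-normal modifier, none of which the protocol gives. The loss could be larger for time since injury and is zero for a step at the cut. Nor does the point touch the primary analysis, where baseline LEMS is a covariate with no banding stated. Even the continuous form leaves interaction power limited.

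**What to change.** In Section 5.4, name as the exploratory interaction analysis the Section 5.2 ANCOVA with two added terms: treatment by continuous baseline LEMS (its main effect is already in the model), and treatment by log months since injury (adding its main effect). Report the estimated treatment effect with its 95% confidence interval across the observed range of each modifier.

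Keep the bands, which for LEMS are the randomisation strata, as a descriptive display. As written they stop at 45, although eligibility has no upper limit on a scale that ends at 50. A continuous term includes every eligible score, but the display needs a band for 46–50.

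The cost is a sentence or two and no new data. The downside is that a linear or log-linear gradient is assumed; it should be checked graphically. Section 6.1 places approval and recruitment in the future, so the text can be changed before any outcome is seen.
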